### Participant Timeline

Recruitment of clinical trial participants began in January 2024 and is scheduled for completion in October 2026. We aim to enroll 10 caregiver-child dyads per quarter who meet all study eligibility criteria. Each family will participate in the trial for a total of 16 weeks, consisting of 12 weeks of active treatment followed by a 4-week posttreatment follow-up.

### Sample Size

The sample size will be 90 caregiver-child dyads, with each dyad randomized to one of three arms: (1) telehealth-delivered SBT (N_1_=30), (2) in-person SBT (N_2_=30), and (3) caregiver online psychoeducation (N_3_=30). Power estimation was based on the primary outcome, the rate of challenging behavior recorded during in-session observations. Power analyses were conducted using mixed-effects modeling, accounting for anticipated attrition of 20% by week 12. Therefore, oversampling beyond the initial total of 90 caregiver-child dyads is not planned.

Preliminary data from our prior study demonstrated a large intervention effect (Cohen *d*=1.5) on the rate of challenging behavior during in-session observations after a 12-week comparable intervention delivered via telehealth [59]. To provide a conservative estimate, we used an effect size of *d*=0.8 for our power estimation. We conservatively assumed an intraclass correlation across repeated measures of 0.7 based on the established test-retest reliability of 0.8‐0.9 for in-session observations of challenging behavior. Under these assumptions, with initial N=30 per group and 20% attrition, the estimated power to detect a significant intervention effect is 0.88 (α=.05, 2-tailed).

We further hypothesize that parenting stress, as measured by the PSI-4-SF, will be significantly lower at the 12-week assessment point among caregivers receiving telehealth-delivered SBT compared with those receiving in-person SBT. As a clinically meaningful minimum effect size, we assumed an effect size (Cohen’s *d*=0.8), which is also supported by previous studies. We assumed a 20% attrition rate by 12 weeks. Under this scenario, the estimated power to detect a group difference is 80% (2-tailed, α=.05) based on a simple group comparison. Power is expected to improve when a longitudinal mixed-effects model incorporating repeated measures is applied.

We will examine caregivers’ implementation fidelity as a potential mediator of reductions in caregiver stress. In the absence of prior data, we assume a medium effect size for the treatment effect on fidelity (eligibility criteria for mediation), yielding 80% power with an initial sample of N=90 dyads and 20% attrition. For the second part (analytical criteria for mediation), we assumed a medium correlation (*r*=0.3) between caregiver fidelity and levels of caregiver stress, which leads to ample power to detect mediation (power=0.96; 2-tailed, α=.05). Again, we will gain power as we conduct the mediation analysis in our mixed-effects modeling framework. Finally, exploratory moderator analyses will emphasize hypothesis generation and clinical significance (effect size) rather than reliance on statistical significance testing (ie, *P* values).

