*Parent Motivation Inventory* (PMI) [58]: The PMI is a 25-item questionnaire measuring parent motivation to participate in treatment. It evaluates the desire for change in their child, the willingness to change their own behaviors to influence the child’s change, and the perceived ability to change those behaviors. The total PMI score will be used to index caregiver motivation at baseline. Secondary exploratory analyses will examine whether baseline caregiver motivation predicts treatment engagement and outcomes, including reductions in caregiver stress and improvements in behavior.

*Barriers to Treatment Participation Scale—Expectancies* (BTPS-exp) [59]: The BTPS-exp is a 44-item questionnaire that assesses perceived treatment barriers across 4 primary areas: stressors or obstacles that compete with treatment, treatment demands and issues, perceived relevance of treatment, and the caregiver-therapist relationship. Total and subscale scores will describe perceived barriers to treatment at baseline. Secondary exploratory analyses will examine whether baseline BTPS-exp scores predict treatment outcomes, including reductions in behavior and caregiver stress and treatment satisfaction.

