### Statistical Methods

In this longitudinal randomized controlled trial (RCT), 90 caregiver-child dyads of children with ASD will be assessed repeatedly at baseline, weeks 4, 8, and 12, and at 4-week posttreatment follow-up, allowing for strong inference regarding the longitudinal relationships among behavioral treatment, treatment fidelity, and challenging behaviors. The core analysis strategy in this project is longitudinal mixed-effects modeling, fully using the repeatedly measured primary and secondary outcomes. For maximum likelihood estimation of mixed-effects models, Mplus will be used. Because caregivers’ fidelity in implementing the same treatment will be observed under both in-person and telehealth conditions, we will examine the mediating effect of treatment fidelity (rather than conducting per-protocol analyses). We will follow the eligibility and analytical criteria of the MacArthur approach to mediator analysis [60], which will be embedded in our mixed-effects models. Specifically, mediation will be examined through two tests: (1) whether treatment via telehealth or in person significantly increases caregiver fidelity (eligibility criterion for mediators) and (2) whether the fidelity is correlated with caregiver stress (analytical criterion for mediators). As part of the sensitivity analysis, we will also use modern causal mediation approaches that use potential outcomes and propensity scores.

We will first estimate the main effect of the intervention on our primary outcomes, the rate of child challenging behavior and caregiver stress, using standard mixed-effects modeling, fully using all available repeated measures (0-, 4-, 8-, 12-, and 16-week follow-up). The primary parameter of interest is the group difference at 12 weeks (end of treatment). We expect that children who receive telehealth-delivered SBT or in-person SBT will show significant decreases in challenging behavior compared with those who receive caregiver online psychoeducation. We further expect that caregivers who receive telehealth-delivered SBT will report significantly lower scores on the total score of the PSI-4-SF than those who receive in-person SBT.

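### The second mediation criterion correlates non-randomised fidelity with the level of caregiver stress and names no baseline adjustment, although the aim is to explain reductions in stress

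*Protocol article*

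**What the plan says.** The mediation paragraph of Sample Size introduces fidelity as "implementation fidelity as a potential mediator of reductions in caregiver stress". It then gives two criteria. The first is that treatment affects fidelity, with a medium effect assumed, "yielding 80% power with an initial sample of N=90 dyads and 20% attrition". The second assumes r=0.3 "between caregiver fidelity and levels of caregiver stress, which leads to ample power to detect mediation" ("power=0.96; 2-tailed, α=.05").

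Statistical Methods repeats the second criterion as "whether the fidelity is correlated with caregiver stress (analytical criterion for mediators"). It says of the mediator approach, "which will be embedded in our mixed-effects models". The main-effect models for the primary outcomes, of which caregiver stress is one, are described as "fully using all available repeated measures (0-, 4-, 8-, 12-, and 16-week follow-up"), so week-0 stress is among the outcomes. Causal mediation methods with potential outcomes and propensity scores are planned as part of the sensitivity analysis.

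Neither section says whether the fidelity term acts on the level of stress or on its change, which covariates accompany it, or which variables enter the propensity scores.

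**The concern.** Randomisation protects the first criterion (arm to fidelity) but not the second (fidelity to stress). Caregiver fidelity is observed after allocation, so its link with stress is observational. A caregiver who enters the trial under heavy stress may implement less well and may also still be stressed at week 12. Fidelity and week-12 stress are then correlated even if fidelity does nothing.

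The aim is about reductions, while the criterion and its power figure are about levels. A level correlation cannot separate the statement that fidelity lowered stress from the statement that less stressed caregivers implemented better.

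The result carries weight. Statistical Methods uses the fidelity mediation in place of per-protocol analyses. Sample Size gives it a powered test at two-sided .05, while the moderator analyses are described as hypothesis-generating.

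**Working it through.** **The plan's own figure.** With N=90 and 20% attrition, 0.8 × 90 = 72 dyads remain. Power for a correlation by Fisher's z is Φ(atanh(r)·√(n−3) − 1.96). For r=0.3 and n=72 this is Φ(0.3095 × 8.307 − 1.96) = Φ(0.611) = 0.73. With all 90 dyads it is 0.82, and with 48 it is 0.55. The stated 0.96 needs about 147 dyads. That is a separate matter, and nothing below depends on it.

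**Inputs for the bias check.**
- n=72 (all arms) and n=48 (the two SBT arms, 0.8 × 60, where fidelity to the same treatment is observed). Both follow from the Sample Size section.
- ρ, the size of the negative correlation between baseline stress and fidelity: 0.1 to 0.4. Assumption; the document gives no figure.
- s, the correlation between baseline and week-12 stress: 0.7. Assumption; the ICC of 0.7 in Sample Size is for in-session behaviour, not for the PSI-4-SF.
- No effect of fidelity on stress. Baseline stress is the only common cause.

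**Formulas** (standardised variables).
- Level: corr(fidelity, week-12 stress) = −ρ·s.
- Change: corr(fidelity, week-12 minus baseline stress) = +ρ·√((1−s)/2). The positive sign means that higher fidelity goes with less reduction in stress.
- Rejection rate ≈ Φ(|atanh(r)|·√(n−3) − 1.96), plus the small opposite tail.

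**Worked example, ρ=0.3, s=0.7.**
- Level: r = −0.21 and atanh(0.21) = 0.2132. At n=72: Φ(0.2132 × 8.307 − 1.96) = Φ(−0.19) = 0.425. At n=48: Φ(0.2132 × 6.708 − 1.96) = Φ(−0.53) = 0.30.
- Change: r = 0.3 × √0.15 = +0.116. At n=72: Φ(0.1167 × 8.307 − 1.96) = Φ(−0.99) = 0.16. At n=48: 0.12.

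**Simulated rejection rates** (100,000 trials per cell, nominal 5%, s=0.7):

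| n | ρ | level | change | baseline stress as covariate |
|---|---|---|---|---|
| 48 | 0.1 | 8% | 6% | 5% |
| 48 | 0.2 | 16% | 8% | 5% |
| 48 | 0.3 | 30% | 12% | 5% |
| 48 | 0.4 | 50% | 18% | 5% |
| 72 | 0.1 | 9% | 6% | 5% |
| 72 | 0.2 | 22% | 10% | 5% |
| 72 | 0.3 | 43% | 16% | 5% |
| 72 | 0.4 | 67% | 26% | 5% |

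With ρ=0.3 and n=72, moving s from 0.5 to 0.8 takes the level rate from 24% to 53% and the change rate from 24% to 12%; the adjusted rate stays at 5%.

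**Direction.** At ρ=0.3 and s=0.7, change-score rejections that suggest fidelity reduces stress occur in only 0.3% (n=48) and 0.2% (n=72) of trials. The rest point the other way.

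**Precision.** Suppose instead a true effect of −0.3 with no confounding and s=0.7. The residual variance given baseline is 1 − 0.49 = 0.51, so the partial correlation is 0.3/√0.51 = 0.42 in size. Fisher's z with one covariate gives power 0.84 at n=48 (against 0.55 unadjusted) and 0.96 at n=72 (against 0.73).

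**The case against.** The strongest reply is that the document is silent on covariates and does not exclude them. It gives each criterion in one clause, embeds them in mixed models, and may leave the model terms to an analysis plan that is not shown. The r=0.3 is a planning input, and Sample Size says that the analysis itself will use the mixed-model framework. This stands in part. A reader might infer that the trial will run the test unadjusted, but the document does not say so. What remains is that the criterion is worded twice as a correlation with stress, once expressly with its level, and that this does not fit the aim stated in the same paragraph.

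Embedding the test in a model that includes week 0 does not settle the matter. Week-0 stress then enters as an outcome, which is not the same as adjusting for it. If the model in effect tests change, the bias is smaller and mostly reversed. So inflated false support for mediation is only one of two possible results.

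The propensity-score sensitivity analysis does address a non-randomised mediator, but its variables are not named and it is secondary to the two stated criteria.

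A reader might also infer that the protocol expects baseline motivation to drive both fidelity and stress. It does not: it will examine "whether baseline caregiver motivation predicts treatment engagement and outcomes, including reductions in caregiver stress", which is an open question, and engagement is not implementation fidelity.

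Nor are the rates above the rates of a false mediation claim. That claim also needs the first criterion to be met, and its stated 80% power does not reproduce by a simple comparison if medium means d=0.5 (24 v 24 gives 0.41; 48 v 24 gives 0.52).

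Finally, mediation by fidelity is not among the stated objectives or listed outcomes, which limits how serious the point is.

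**Conclusion.** The point holds as a mismatch between a stated test and its stated aim, with no baseline term named. It does not show that baseline stress will be left out. If fidelity is related to baseline stress, the criterion as worded is biased: about 8% to 50% rejection at 48 completers and 9% to 67% at 72 for a level correlation, or about 6% to 26%, mostly in the wrong direction, for a change from week 0. These figures rest on assumed correlations and on a single-time-point simplification of the mixed model. If fidelity is unrelated to baseline stress, there is no bias. If more stressed caregivers implement better, the sign of the bias turns round.

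Adjusting for baseline stress restores the 5% rate under these assumptions whichever form the model takes, and it adds precision when the effect is real. It does not remove confounding by other, unmeasured causes. The change is worth making while recruitment is still open and analysis has not begun.

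**What to change.** In the mediation paragraph of Sample Size and in Statistical Methods, restate the analytical criterion as the effect of caregiver fidelity on post-baseline PSI-4-SF total, with the week-12 effect as the parameter, estimated in the planned longitudinal mixed model with arm and baseline PSI-4-SF total as covariates. Keep the week 4 and week 8 data in the model. A week-12-only regression would discard the earlier measurements of dyads that discontinue, who are not assessed further. Name baseline PSI-4-SF total among the variables of the causal mediation sensitivity analysis as well. Adding baseline PMI total is optional.

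The cost is wording and one degree of freedom, because baseline PSI-4-SF is already collected. If a statistical analysis plan already adjusts for baseline stress, only these two sections need to be aligned with it.

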### Trial Design

The Caregiver Outreach Autism Coaching at Home study is a single-site, multiarm, parallel-group, randomized controlled superiority trial targeted to decrease challenging behaviors in children with ASD. We aim to recruit 90 caregiver-child dyads to participate in the 4-year study. Each dyad will first receive a practical functional assessment (PFA) to identify the function(s) of the child’s challenging behavior and subsequently randomized (1:1:1) to telehealth-delivered SBT, in-person SBT, or online psychoeducation.

The primary outcome will be in-session rates of challenging behavior observed at the 12-week outcome point, measured through standardized behavioral observation procedures as well as reported levels of caregiver stress. Secondary outcomes will include family quality of life, treatment satisfaction, and indicators of sustained family engagement and continuity of care, reflected by the number of scheduled sessions completed, missed appointments, and participant attrition at the 12-week outcome (end of treatment). A SPIRIT (Standard Protocol Items: Recommendations for Interventional Trials) diagram showing the schedule of enrollment, interventions, and assessments is shown in he overall study is shown in Figure 1. The study flowchart is shown in Figure 2. For all participants, in-session observations and parent questionnaires will be conducted at 5 assessment points: baseline (T0), 4 weeks (T4), 8 weeks (T8), 12 weeks (T12), and 16 weeks (T16). The study protocol (version 1.9; May 8, 2025) follows the SPIRIT statement. The trial has been registered at ClinicalTrials.gov (identifier: NCT05268796). All methods were finalized before enrollment began. Subsequent protocol revisions included decreasing the lower bound of the age range to include children aged 2 years and including additional rural counties in New Mexico to increase the reach of the study.

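### Stated power of 0.96 for the fidelity–stress correlation is about 0.73 on the plan's own inputs, and the 80% for the fidelity effect cannot be reproduced at a conventional medium effect

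*Protocol article*

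**What the plan says.** The last paragraph of Sample Size powers the mediation analysis in two steps. For the first, the assumption reads "we assume a medium effect size for the treatment effect on fidelity (eligibility criteria for mediation"). No number is attached to medium. The result claimed for this step is worded as "yielding 80% power with an initial sample of N=90 dyads and 20% attrition". For the second, a correlation of 0.3 between fidelity and stress is assumed and called medium, "which leads to ample power to detect mediation (power=0.96; 2-tailed, α=.05"). The paragraph then says that carrying out the mediation analysis within the mixed model will add power.

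Statistical Methods defines the two tests. The first asks "whether treatment via telehealth or in person significantly increases caregiver fidelity (eligibility criterion for mediators"). The second, which is the one given power of 0.96, asks "whether the fidelity is correlated with caregiver stress (analytical criterion for mediators").

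The design is three arms, "subsequently randomized (1:1:1) to telehealth-delivered SBT, in-person SBT, or online psychoeducation", 30 dyads each, with power calculations "accounting for anticipated attrition of 20% by week 12".

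**The concern.** Every input to the 0.96 figure is in the text: the correlation, the significance level, two-sidedness, the sample and the attrition. A correlation of 0.3 is not normally detectable with 96% power in a sample of this size, so the figure needed checking. The 80% looked doubtful for the same reason, because about 24 completers per arm is few for a medium effect.

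At stake is how a non-significant mediation test will be read. At power 0.96 the chance of missing a true r = 0.3 is 4%; at 0.73 it is 27%. Someone relying on the published figure would give a null result more weight than it deserves. The same paragraph describes the moderator analyses as hypothesis-generating but puts no such caution on mediation.

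**Working it through.** **Inputs.** From Sample Size and Trial Design: N = 90, 30 per arm, attrition 20%, r = 0.3, two-sided α = 0.05. Completers: 90 × 0.8 = 72, or 24 per arm. Both SBT arms pooled versus control is 48 v 24; one arm versus another is 24 v 24. Assumption: medium means d = 0.5, the usual convention and the counterpart of calling r = 0.3 medium.

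**Fidelity–stress correlation (stated 0.96).** Fisher z: power ≈ Φ(atanh(r) × √(n − 3) − 1.96), with atanh(0.3) = 0.3095.

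- n = 72: 0.3095 × √69 = 2.571; 2.571 − 1.960 = 0.611; power 0.73.
- n = 90 (no attrition): 0.3095 × √87 = 2.887; 2.887 − 1.960 = 0.927; power 0.82.
- n needed for 0.96: ((1.960 + 1.751) / 0.3095)² + 3 ≈ 147 completers, or 147 / 0.8 ≈ 184 enrolled.
- r needed for 0.96 at n = 72: tanh((1.960 + 1.751) / √69) = tanh(0.447) ≈ 0.42.

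The method makes little difference: the noncentral t gives 0.75 at n = 72 and 0.84 at n = 90, and simulation gives 0.74 and 0.83.

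Attempts to recover 0.96:

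| Variant | Power |
|---|---|
| One-sided, n = 90 | 0.89 |
| 72 completers, 5 measures, ICC 0.7 (effective n = 72 × 5 / 3.8 = 94.7) | 0.84 |
| 72 completers, 5 measures, ICC 0.5 (effective n = 72 × 5 / 3 = 120) | 0.92 |
| f² = 0.15 (r about 0.36) instead of r = 0.3, n = 90, no attrition | 0.953 |

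The ICC of 0.7 is stated only for in-session behaviour; 0.5 is a sensitivity value. The last row comes close, but only by changing the stated correlation and ignoring attrition.

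**Treatment effect on fidelity (stated 80%).** Normal approximation: power ≈ Φ(d × √(n₁n₂ / (n₁ + n₂)) − 1.96).

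- 48 v 24, d = 0.5: √16 = 4; 0.5 × 4 − 1.96 = 0.04; power 0.52 (0.51 by noncentral t).
- 24 v 24, d = 0.5: √12 = 3.464; 1.732 − 1.96 = −0.228; power 0.41 (0.40 by noncentral t).

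Range by noncentral t:

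| d | 48 v 24 | 24 v 24 |
|---|---|---|
| 0.5 | 0.51 | 0.40 |
| 0.6 | 0.66 | 0.53 |
| 0.7 | 0.79 | 0.66 |
| d giving 80% | 0.71 | 0.83 |

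A three-arm F test with f = 0.25 and N = 72 gives 0.44. Without attrition, 60 v 30 at d = 0.5 gives 0.60.

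**Comparison within the same section.** The parenting-stress power (d = 0.8, 24 v 24, stated 80%) gives 0.8 × 3.464 − 1.96 = 0.811, power 0.79 (0.77 by noncentral t). That roughly matches its stated figure, so a simple calculation on completers is how that figure was reached. The mediation figures do not follow in the same way.

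**The case against.** The strongest objection concerns the 80%. The text never says what medium means, and the section elsewhere calls 1.5 large and 0.8 conservative, so it does not fix medium at 0.5. At about d = 0.71 the 48 v 24 comparison does reach 80%. Adjusting for a baseline measure correlated 0.7 with the outcome would also reach 0.80 at d = 0.5, though the article states no such adjustment for fidelity. This stands: a reader might infer that the 80% is simply wrong, but the article supports only that it cannot be reproduced at the conventional value and that the number behind it is not given.

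A second objection is that repeated measures could supply the missing power for the correlation. This does not stand. The mixed-model gain is presented as coming on top of the stated figures, and at ICC 0.7 it would bring power only to about 0.84.

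Third, mediation is outside the primary and secondary objectives, and N was set on the primary behaviour outcome. That stands and limits the importance of the point.

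Some stronger readings are tempting but not supported:

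- **Only the two SBT arms count.** The remark "Because caregivers’ fidelity in implementing the same treatment will be observed under both in-person and telehealth conditions" might suggest 48 completers and still lower power. It explains why mediation is studied, not who is analysed. The power paragraph uses 90 dyads, control caregivers have probe sessions, and fidelity collection is not restricted to the SBT arms.
- **The two powers can be multiplied into a joint power.** That would need the tests to be independent and d = 0.5; the article gives neither.
- **The power figures justify mediation over a per-protocol analysis.** The reason given is that fidelity is observed under both delivery modes; power is not mentioned.
- **The second test is a bare pooled correlation.** The article embeds the criteria in mixed models and adds causal-mediation sensitivity analyses; exact model terms may properly sit in an analysis plan that is not shown.
- **The figures belong to a trial twice as large.** Both do reproduce at 144 completers (96 v 48 at d = 0.5 gives 0.80; r = 0.3 gives 0.957), which is 80% of 180. Nothing in the article says so.

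**Conclusion.** The 0.96 is wrong on the stated inputs: the power is about 0.73 at 72 completers and 0.82 at most if nobody drops out. This rests only on r = 0.3, two-sided 5%, 90 dyads and 20% attrition. The sentence giving 0.96 does not repeat the sample size, but the preceding sentence supplies it and no variant tried that keeps r = 0.3 and N of at most 90 reaches 0.96.

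The 80% is a conditional finding. With d = 0.5 assumed, power is about 0.51 (pooled) or 0.40 (pairwise); 80% for the pooled contrast implies d of about 0.71, larger than what is usually called medium.

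Describing the power as ample is therefore unsupported. The error is confined to a non-primary analysis and leaves the sample size and the primary analyses untouched. It is worth correcting because it is a misstated figure that is cheap to put right.

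**What to change.** In the last paragraph of Sample Size:

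1. Replace 0.96 with about 0.73 for r = 0.3 at 72 completers, or keep 0.96 and state that it applies to a detectable r of about 0.42.
2. Delete the word ample.
3. For the fidelity effect, state the numeric effect size and the contrast. Either give about 0.5 as the power at d = 0.5 (48 v 24), or keep 80% and state that it requires d of about 0.71 for that contrast. If baseline adjustment or averaging over visits lies behind the 80%, state the correlation used.

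The change is to wording only. Its cost is a less favourable stated power for the mediation analysis; no change to recruitment, N or the primary analyses is needed. Analysis is not due to start until Winter 2026, so the correction can be made beforehand.
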